#### Aim II. Examine the underlying mechanisms of ACT over 6 months

Aim II involves the following hypotheses 2a–2c:

*Hypothesis 2a*. Linear mixed-effects models similar to the ones developed in H1 will be fit for AD signature cortical thickness, functional connectivity in the DMN, and aerobic fitness. We will obtain the model-based estimates of the change in these mechanistic measures by randomized groups to determine which group had the largest change, and we will conduct a composite hypothesis test to assess if the changes in aerobic fitness at 3 and 6 months and in AD signature cortical thickness and DMN at 6 months differ significantly by group.

*Hypothesis 2b*. We will consider the same linear mixed-effects models as in H1 but will include changes in AD signature cortical thickness, functional connectivity in the DMN, and aerobic fitness at the corresponding time point in the models. Because of likely collinearity in these measures, separate models will be fit for each measure.

*Hypothesis 2c*. We will fit a longitudinal mixed-effects model (similar to H1) for the change in cognition, which will include both the change in aerobic fitness and the mediator’s changes in AD signature cortical thickness and functional connectivity, and longitudinal mixed-effects models for the changes in AD signature cortical thickness and functional connectivity that include aerobic fitness as a predictor. The estimated controlled direct effect and natural indirect effect can then be easily derived from the estimated coefficients of these models.

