### Study aims

The purpose of this phase II RCT is to test the efficacy and additive/synergistic effects of an ACT intervention (cycling and SOP training), by comparing it to cycling and SOP training alone and an attention control (stretching and mental leisure activities), on cognition and relevant mechanisms (aerobic fitness, AD signature cortical thickness, and DMN) in older adults with amnestic MCI (aMCI). Here we choose AD signature cortical thickness [49] and DMN [50] since they are common neural markers detected early in the progression of AD. The study is funded by the NIH’s National Institute on Aging (R01AG055469-01A1, 9/15/2017–5/31/2022). The specific aims and hypotheses of the study are described as follows:Aim I. Determine the efficacy and additive/synergistic effects of ACT on cognition over 6 months

*Hypothesis 1*. ACT will have the greatest effects on executive function and episodic memory compared with other groups.Aim II. Examine the underlying mechanisms of ACT over 6 months

*Hypothesis 2a*. ACT will have the greatest effects on AD signature cortical thickness, functional connectivity in the DMN, and aerobic fitness compared with other groups.

*Hypothesis 2b*. Changes in the mechanistic measures are related to cognitive changes.

*Hypothesis 2c*. Changes in AD signature cortical thickness and DMN mediate aerobic fitness effects on cognition.Aim III (exploratory). Calculate the long-term effect sizes of ACT on cognition and clinical AD conversion to inform future phase III RCTs

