### Statistical analyses

All variables will be summarized using appropriate descriptive statistics (e.g., means/SD for continuous measures, and frequencies for categorical variables). Baseline variables will be compared among the four groups to determine systematic differences using Pearson’s chi-square test (categorical variables) and analysis of variance (ANOVA) or Kruskal-Wallis (continuous variables), as appropriate. Variables that differ significantly among groups will be included as covariates in the models described below. All analyses will follow the intention-to-treat principle (e.g., group assignment in the analysis will be based on randomized group assignment regardless of level of adherence to provide unbiased comparisons of the effects among the groups). This principle will account for any potential data loss. Because Aims I and II focus on cognition and mechanisms, they will be analyzed regardless of MCI clinical phenotype. We will also compare implementation consistency between sites using Pearson’s chi-square test.

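### H2c derives a causal indirect effect from non-randomised changes in fitness and MRI measures, but the stated covariate rule looks only at balance among arms, so the effect is not protected from confounding

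*Protocol article*

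**What the plan says.** Under Study aims, H2c is a mediation hypothesis: "Changes in AD signature cortical thickness and DMN mediate aerobic fitness effects on cognition". H2b, beside it, is worded as association: "Changes in the mechanistic measures are related to cognitive changes".

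The Aim II part of Statistical analyses gives H2c two sets of models. One is a model for change in cognition, "which will include both the change in aerobic fitness and the mediator’s changes in AD signature cortical thickness and functional connectivity". The other is "longitudinal mixed-effects models for the changes in AD signature cortical thickness and functional connectivity that include aerobic fitness as a predictor". It then concludes: "The estimated controlled direct effect and natural indirect effect can then be easily derived from the estimated coefficients of these models".

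These models are described as similar to H1. The H1 model (Aim I) has visit, group, their interaction and a random participant effect. Covariates enter through one rule, given in the opening paragraph of Statistical analyses: "Variables that differ significantly among groups will be included as covariates in the models described below". Aim I restates it more loosely: imbalanced covariates may be included, with stepwise selection by AIC. The Covariates section lists variables chosen for a known relationship with cognition, but explains the limits of the list by the balance that randomisation brings. It does not assign them to the Aim II models. The Discussion adds that analyses will incorporate design features, naming site.

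**The concern.** In H2c the exposure is change in fitness, not the assigned arm, and the mediators are changes in MRI measures. Participants are not randomised to any of these. Reading a controlled direct effect and a natural indirect effect off the coefficients requires no uncontrolled common cause of fitness and cognition, of fitness and the MRI measure, or of the MRI measure and cognition. The article does not state that condition.

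The covariate rule suits a different question. Imbalance among arms matters for comparing arms, as in H1 and H2a. A variable can be perfectly balanced among the four arms and still, within every arm, drive fitness change, atrophy and cognitive change together. Education, premorbid intellect, and baseline cognition, fitness and brain structure are candidates, and all are collected. Under the rule they would usually be left out because randomisation had worked. Aim II could then report neural mediation of a fitness effect where the three changes merely share a cause.

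**Working it through.** The protocol gives no figure for this point, so there is none to reproduce. The check asks what the stated rule does when a balanced common cause exists.

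**Inputs**
- n = 96 at 6 months, or 24 per arm (Sample size and power: 128 × 0.75 = 96).
- Type I error 0.05 (same section); two-sided is assumed.
- One time point: within the 6-month window, post-baseline MRI exists only at month 6 (Table 2).
- Assumed: one baseline factor, independent of arm, with correlation r to each of the three changes. There is no other link among them within arm, so the true indirect effect is zero. The protocol gives no value for r, so a range is shown.
- Mediation is declared when both paths are significant.

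**Step 1: how often the rule admits the factor.** The factor is independent of arm, so its test for imbalance rejects at its own size, about 5%, however strongly it confounds. Simulated selection was 4.7% to 5.6%.

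**Step 2: spurious effect with group alone in the model.** The common cause gives each pair of changes a within-arm correlation ρ = r². The fitness-to-MRI path is a = ρ. The MRI-to-cognition path given fitness is b = (ρ − ρ²)/(1 − ρ²) = ρ/(1 + ρ). The false indirect effect is a × b. At r = 0.5: ρ = 0.25, b = 0.25/1.25 = 0.20, a × b = 0.050 (simulated 0.051).

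**Step 3: how often it is declared significant.** By Fisher's z at r = 0.5:
- Path a, given group (3 df): atanh(0.25) × √(96 − 3 − 3) = 0.255 × 9.49 = 2.42, and Φ(2.42 − 1.96) = 0.68.
- Path b, given group and fitness (4 df): atanh(0.20) × √(96 − 4 − 3) = 0.203 × 9.43 = 1.91, and Φ(1.91 − 1.96) = 0.48.
- Both: 0.68 × 0.48 ≈ 0.33 (simulated 32%).

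**Step 4: the planned rule.** The factor is omitted in about 95% of trials and adjusted for in about 5%: 0.95 × 32.4% + 0.05 × 0.2% = 30.8% (simulated 31%).

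| r | False indirect effect, a × b | False mediation, group only | Planned rule | Factor always adjusted for |
|---|---|---|---|---|
| 0 | 0 | 0.2% | 0.2% | at most 0.3% |
| 0.3 | 0.09 × 0.083 = 0.007 | 1.7% | 1.5 to 1.6% | at most 0.3% |
| 0.4 | 0.16 × 0.138 = 0.022 | 8 to 9% | 8 to 9% | at most 0.3% |
| 0.5 | 0.25 × 0.200 = 0.050 | 32% | 31% | at most 0.3% |
| 0.6 | 0.36 × 0.265 = 0.095 | 69% | 66% | at most 0.3% |

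The planned-rule column barely differs from adjusting for group alone. Requiring both paths makes the test conservative, so the benchmark without confounding is about 0.2%, not 5%.

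**Step 5: age as the common cause.** If the factor is age and a two-level age stratum is in the model (median split assumed), false mediation falls to about 0.8% at r = 0.4 and about 2.6% at r = 0.5.

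**The case against.** Several points on the other side are sound.

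- **H2b.** A reader might infer that H2b makes the same causal error and produces false positives. The document does not support that. H2b claims only that the changes are related, and a shared cause makes that true. The point reaches H2b only where its result is interpreted as mechanism.
- **Existing adjustment.** A reader might infer that the models contain nothing except imbalanced covariates. Group and visit are in them, and site is promised. Randomisation is stratified by age below 75 or not (Design), so the age stratum may also enter as a design feature, although the Discussion does not name it. Step 5 shows this would remove most of the problem if age were the confounder. It does nothing for education, premorbid intellect or baseline status.
- **Size.** A reader might infer that the indirect effect is shown to be confounded. It is not. At r = 0.5 a single omitted variable must explain 25% of the variance in each of three changes, and the protocol gives no such figure.
- **Deferral.** A full confounder list and sensitivity analyses commonly sit in the full protocol or SAP, and their absence here is no fault. But the article does state the inclusion rule, justify its limited list by randomisation, and assert that "The estimated controlled direct effect and natural indirect effect can then be easily derived" from the coefficients. An SAP that followed it would carry the problem forward.
- **Time ordering.** The visit schedule offers no clean remedy. Fitness change over 0 to 3 months lies inside MRI change over 0 to 6 months, and month-12 cognition is reserved for Aim III.

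**Conclusion.** The point holds for H2c. The plan claims causal effects from non-randomised exposure and mediators, and selects covariates by a criterion unrelated to within-arm confounding. The conclusion is that the indirect effect is unprotected, not that it is known to be biased. Under the assumptions in the working, the risk is small at r = 0.3, material at r = 0.4 and serious at r = 0.5 or above; the arm-imbalance rule removes almost none of it. These figures rest on assumed correlations, a single common cause and a single time point. The randomised comparisons in H1 and H2a are untouched. The change is worth making because the protection is available from data already collected.

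**What to change.** For the H2c models, and for H2b wherever it is interpreted as mechanism, replace the arm-imbalance rule with a prespecified set of baseline confounders, included whatever their balance among arms and not subject to stepwise selection. The set is continuous age, sex, education, premorbid intellect, and baseline fitness, MRI measure and cognition, in addition to group, visit and site. Because the H2c outcome is change in cognition, and adjusting change for its baseline value is a debated choice, the text should say explicitly how baseline cognition enters.

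Replace the statement that the effects are easily derived with one that reports the direct and indirect effects as conditional on no unmeasured confounding of exposure, mediator and outcome. If that assumption is not to be made, report H2c as associations.

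The cost is wording plus degrees of freedom. The seven added terms (eight if both MRI measures share a model), with three for group and one for site, make about 11 or 12 parameters before visit terms and mediators, on about 96 participants. No new data are needed.

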#### Aim III. Calculate the long-term effect sizes of ACT on cognition and clinical AD conversion to inform future phase III RCTs

Effect sizes for cognition and mechanisms will be calculated using effect-size equations similar to those proposed in Aim I. Time to AD conversion and reversion to normal from randomization will be compared among groups using log-rank tests. In addition, using the model developed in Aim I, we will compute the within-group model-based average changes for each cognitive outcome at 12 and 18 months for each group and conduct a composite hypothesis test to assess group differences in cognitive changes at 12 and 18 months.

### Ethics

This study was approved by the IRBs at both UMN and UR as well as by the DSMB. Any subsequent changes or amendments to the protocol will be submitted to the IRBs and DSMB for approval. Initial consent takes place during step 2, the in-person interview. The staff will assess the participant’s capacity to consent using the UCSD Brief Assessment of Capacity to Consent (UBACC) form modified for the ACT trial. A participant must score a 2 on items 1, 2, 4, 6, 7, and 9 on the assessment for inclusion in the study. If a participant scores less than 2 on any of these items, the staff will re-explain the study and then ask the participant to return on another day to re-take the UBACC. If the participant scores less than 2 on any of these items again, then the subject is not eligible to participate in the study.

Consenting will be an ongoing process during the study. Verbal consent will be obtained at the beginning of each activity session and during the monthly assessment of activity participation during the 1-year follow-up period. Signed paper consent will be obtained prior to subsequent data collections. The participants’ capacity to consent will be re-assessed at 12 and 18 months, prior to data collection, as in the in-person screening. Consent at data collection visits (12 and 18 months) will be conducted similarly to initial consent. Surrogate consent will be obtained for participants who lose the capacity to consent from their representative (i.e., caregiver), and assent from the participant will be noted on the form. Representatives will be identified in order of priority (e.g., durable power of attorney for health care, court-appointed guardian for health care decisions, spouse, and adult child). We will only follow up with the participants who provide consent/assent.

In the event that subjects suffered research-related injury, treatment will be available, including first aid, emergency treatment, and follow-up care as needed. However, care for such injuries during and after the study period will be billed in the ordinary manner to the subjects and their insurance companies.

### Dissemination

Findings from the study will be disseminated through publications and presentations. Participants and their family members will receive a copy of the published main findings. Authorship will follow the established publication guidelines such as those of the International Committee of Medical Journal Editors. We do not intend to use professional writers. Access to the final trial data set will follow the guidelines of the NIA.

## Discussion

The RCT is the gold standard design for determining the causal effect of an intervention on an outcome. Alternative designs include cross-over and usual care or waitlist as controls. Cross-over designs are ideal for interventions without carry-over effects, which is not the case for ACT. Usual-care or waitlist controls preclude assessing the placebo or Hawthorne effect of ACT.

A potential problem is unblinding. We have built in four strategies to ensure blinding: randomization using permuted blocks; all investigators blinded to group assignments; all participants blinded to the study aims and reminded as needed not to discuss their experiences with the outcome assessor; and outcome assessors blinded to the study aims, group assignments, and previous test results, and interacting with participants only for data collection [52]. Assessors will not interact with other staff who are not blinded (e.g., exercise interventionists) and will participate in separate meetings. Blinding success will be assessed after each data collection: Was group assignment unveiled? Why? For participants whose group assignments are revealed, a different blinded assessor will collect subsequent data. Other strategies include the use of standardized protocol, operations manual, forms, and reliable and valid variable measures. The analyses will incorporate all design features (e.g., site, repeated measures within persons, missing data).

While our aims are not focused on age and sex, we will take two measures to ensure adequate attention to them. First, we will stratify enrollment by age and target an enrollment of 60% women, because age and gender are established risk factors for AD [66]. Second, we will conduct an exploratory analysis examining whether age and sex moderate intervention effects on outcomes. We do not intend a fully powered analysis of this question for this RCT. However, large age/sex differences may be discernible and generate hypotheses for subsequent studies.

We do not plan to emphasize single-domain vs. multiple-domain MCI phenotype when identifying our sample given the change of emphasis in the updated NIA-Alzheimer’s Association (AA) criteria [3, 67]. However, we will secondarily examine the effect of the intervention on these phenotypes to specify a subsample who may benefit, particularly if the proposed intervention is effective for improving primary cognitive outcomes.

The multi-site design is advantageous compared to a single-site design to ensure timely enrollment, reduce regional influences on study implementation and results, increase sample representativeness, and enhance the generalizability of the study findings. A potential problem is differential implementation across our two sites. We have co-created the study protocol, materials, and operations manual and cross-trained investigators and staff via conference calls, video streaming, and site visits. We will implement additional strategies to ensure implementation consistency, including quarterly consistency checks, regular cross-site meetings, and treatment fidelity checks.

In summary, the ACT trial will be the first RCT to examine the additive/synergistic effects of a novel ACT intervention on cognition and relevant mechanisms in aMCI and to advance AD prevention research by providing precise immediate and long-term effect-size estimates of ACT to inform future fully powered, large-scale phase III RCTs.

## Trial status

The status of the trial at the time of manuscript submission is open for enrollment, and we expect enrollment accrual to complete in 2021.

## Abbreviations

ACT: Combined Aerobic exercise and Cognitive Training
AD: Alzheimer’s disease
ADAS-Cog: Alzheimer’s Disease Assessment Scale-Cognition
ADL-PI: Activities of Daily Living-Prevention Instrument
ADNI: Alzheimer’s Disease Neuroimaging Initiative
ANCOVA: Analysis of covariance
BOLD: Blood oxygen level-dependent (signal)
BVMT: Brief Visuospatial Memory Test
DSMB: Data Safety and Monitoring Board
FLAIR: Fluid-attenuated inversion recovery
HR: Heart rate
IADL: Instrumental activities of daily living
IRB: Institutional Review Board
ISWT: Incremental Shuttle Walk Test
MCI: Mild cognitive impairment
MLA: Mental leisure activity
MoCA: Montreal Cognitive Assessment
MPRAGE: Magnetization-prepared rapid gradient echo imaging
MRI: Magnetic resonance imaging
NIA: National Institute on Aging
NIH: National Institutes of Health
PASE: Physical Activity Scale for the Elderly
PSMS: Physical Self-Maintenance Scale
RA: Research assistant
RAVLT: Rey Auditory Verbal Learning Test
RCT: Randomized controlled trial
RPE: Rating of Perceived Exertion
SD: Standard deviation
SOP: Speed of processing
UBACC: UCSD Brief Assessment of Capacity to Consent
UMN: University of Minnesota
UR: University of Rochester
WHODAS: WHO Disability Assessment Schedule
WTAR: Wechsler Test of Adult Reading
